### Additional data

We collected other participant characteristics via in-person questionnaires in tablets using Open Data Kit (ODK Collect 1.4.5, UK) [42]. Other sources of potential air pollution exposure were assessed by asking about smelling smoke from neighboring homes and exhaust from traffic and about practices of trash burning and kerosene use for lighting. Women were asked each visit about their smoking status and exposure to secondhand smoke.

Use of all cookstoves in the household was estimated by logging temperature with electronic cookstove use monitors (SUMs; Thermochron iButtons, Embedded Data Systems, Lawrenceburg, KY, USA). Up to 4 SUMs were deployed per household, depending on the number of cookstoves used. The SUMs could record a range in temperature from 0 to 125 °C and were programmed to log every 5 min for the full 24 h of exposure monitoring. SUMs were placed on chimneys of cookstoves using a harness and silicone buffer to prevent overheating, and if no chimney was present, then SUMs were affixed to a stone and placed near the top of the “U” shape of the chamber (Fig. 4).

**Fig. 4 Fig4:**
[figure not shown]
Examples of SUMs on the chimney of a primary traditional cookstove (**a**) and a secondary traditional cookstove (**b**), circled in red

Additional stove use and cooking behaviors were measured through self-report in the questionnaires, such as time spent cooking on all stoves and separately for animals, recent use of all stoves, and cooking preferences and opinions. Researchers also completed a separate questionnaire with direct observation to capture maintenance and changes to the *Justa* cookstove.

Household elevation and GPS coordinates were collected at baseline and repeated only if the woman had moved houses during the study. Kitchen characteristics were evaluated by size (height, length, and width), drawn diagrams, housing construction materials (e.g., floor, roof, and wall type), location, and ventilation. Ventilation was measured by number of doors and windows, gaps in the walls (yes/no), eaves between the walls and ceiling (none, less than 30 cm, more than 30 cm), and enclosure status (enclosed, semi-open, open). All kitchen characteristics were collected at baseline and repeated if the kitchen had been changed from the previous visit.

Women’s socioeconomic status and demographic characteristics were estimated through household income sources (agriculture only or agriculture with other sources, such as textiles, selling prepared food, owning a food stand, etc.), household material wealth (number of beds per person for the household and ownership of a bicycle, car, motorcycle, television, radio, refrigerator, cell phone, computer, or sewing machine), household electricity, education (highest level of school completed), age (confirmed by national ID card), and household size. Women also self-reported illnesses, previous doctor diagnoses, medication and vitamin use (confirmed by looking at the bottle or prescription label), 24-h dietary recall and diet diversity from 11 food categories, total years of cooking, physical activity, pregnancy (at screening and each visit), and age of youngest child (to help estimate if she had been unknowingly pregnant in the previous study visit) (Table 2).

Physical activity was estimated as self-reported hours per week (hours per day * days per week) for the following 10 lifestyle activities common to our study population: cut wood, grind corn, wash clothes, milk the cow, work in the field, walk moderately outside the house, cook, clean the house, sit relaxed, and sleep. For each activity, the number of hours per week was multiplied by the corresponding Metabolic equivalent (MET) from the Compendium of Physical Activities (Additional file 3: Table S1) [43]. The values were summed to generate the final score. Descriptions of the activity with its equivalent MET score can be found in Supplemental Materials (Additional file 3: Table S1).

In order to assess dietary intake and dietary diversity, women were asked to report everything they ate and drank in the last 24 h and the number of portions for each item. Our questionnaire listed 20 commonly consumed Honduran food items with photo examples (Additional file 4: Table S2) [44]. A dietary diversity score (DDS) represents the number of food groups consumed over a 24-h period, although the specific number of food groups can vary between populations [45]. We calculated DDS by collapsing the 20 food items into 11 groups: grains (corn, cereals, rice, chips), pulses and nuts (nuts, beans), roots (potatoes), other vegetables, fruits, sweets, eggs, dairy (cheese, milk), meat (beef, chicken, pork, fish), oils, and beverages (coffee, soda, juice). The total DDS was a sum of the dichotomous 11 food groups consumed in the past 24 h, with a minimum score of 1 and maximum of 11. Other studies show DDS to vary by socioeconomic status, food availability, and seasonal changes, especially in low- and middle-income countries (LMIC) [44–46].

### Statistical analysis

We will conduct a descriptive analysis of the exposures, health endpoints, and other measured characteristics (Table 2). Quantitative summaries will include means, standard deviations, ranges, and frequencies as appropriate for the data type. Descriptive statistics will be utilized to assess the similarity of participant characteristics across study arms.

Primary analyses will evaluate the association between assigned cookstove type and the 3 primary health endpoints (blood pressure, CRP, HbA1c) in an intent-to-treat framework. We will use a linear mixed model with a fixed effect for assigned cookstove type (traditional or *Justa*), the independent exposure variable of interest. The model will include a random effect for each participant to account for correlation from repeated measures within person. To account for potential changes in the outcomes over time the model will include visit date using a spline trend function. Letting *Y*_*ij*_ denote the health endpoint measurement for participant *i* at visit *j*, *x*_*ij*_ denote the assigned cookstove type (0 for traditional, 1 for *Justa*) for participant *i* at visit *j*, and *t*_*ij*_ denote the time of visit *j* for participant *i*, this model can be written:1$$ {Y}_{ij}=\mu +{a}_i+\beta {x}_{ij}+f\left({t}_{ij}\right)+{\epsilon}_{ij}. $$

In Eq. (1), *β* represents the intervention effect on the outcome measure and is the primary quantity of interest. The parameter *μ* represents the overall average outcome value, *a*_*i*_ represents the random effect for participant *i*, and *ϵ*_*ij*_ is an independent error term. We will use natural cubic splines as the function of time *f* in the model, with the complexity of the adjustment controlled by the number of spline functions.

For the exposure-response analysis, we will use a linear mixed model similar to the model used in the intent-to-treat analysis. In this framework, the personal and kitchen PM_2.5_ measurements will be included as the exposure variable *x*_*ij*_ in Eq. (1). As the exposure-response approach will not utilize the study’s randomization to control for confounding, potential confounders identified a priori will be included in Eq. (1) as additional fixed effect terms. Potential confounders include participant age, indicators of socioeconomic status (e.g., household possessions, participant education level, beds per person in each household), physical activity levels, BMI, and dietary intake. We will also conduct a “per protocol” analysis using self-reported actual cookstove use, rather than assigned cookstove.

We will evaluate effect modification by adding the following variables as interaction terms with the stove assignment or exposure measurement variable in separate models: age (< 40 or ≥ 40 years), blood pressure (normal systolic < 120 and diastolic < 80 vs. borderline high/high systolic ≥ 120 or diastolic ≥ 80), diabetes status (normal hbA1c < 5.7% vs. pre-diabetic/diabetic ≥ 5.7%), BMI (normal < 25 or overweight/obese ≥ 25), waist circumference (< 80 cm vs. ≥80 cm), and metabolic syndrome (presence vs. absence).

Sensitivity analyses will be conducted to assess the impact of different forms of the adjustment for time in Eq. (1) by varying the number of spline functions and considering alternative representations such as indicators of season or visit number. We will also conduct sensitivity analyses that exclude women who were taking medications that could influence inflammation in the body, such as hypertension or vitamins, or who were ill at the time of the health measurements. Additional sensitivity analyses will exclude air pollution samples that came from pumps that ran for less than 24 h, and flow rates that strayed outside the 10% pre- and post-sampling range.

The sample size of 230 was selected based on feasibility and cost considerations and is well-powered for the primary analyses. We estimated power by conducting a simulation that generates data according to the study design and Eq. (1). For the blood pressure model: assuming a standard deviation of 12 mmHg for systolic blood pressure [26], a correlation of 0.76 between repeated measures from the same individual [47], and a 10% loss to follow-up, we estimate there will be 80% power to detect a difference of 1.81 mmHg. This difference is smaller than that observed in the only cookstove randomized controlled trial conducted among non-pregnant women in Guatemala [7]. The power remained constant adding linear trends of 3 mmHg/year and seasonal trends of amplitude 3 mmHg to the simulated blood pressure measurements. For the CRP model: assuming a standard deviation of 1.1 mg/dL [48], a correlation of 0.66 [49] between repeated measures from the same individual, and a 10% loss to follow-up, we estimate there will be 80% power to detect a difference of 0.2 mg/dL. Although different cooking fuels and sources of indoor pollution were investigated, this difference in CRP is similar to that observed in a random crossover design evaluating the impact of indoor air filtration among homemakers in Taiwan [50].

For missing data, we will record the number, timing, pattern, and reason. Missing data may occur due to subject-initiated drop out, missing visits, instrument failure, and data entry error. We will evaluate whether the missing data patterns are differential between study arms, or by study visit. For all analyses, we will assume missing data to be missing at random a priori.

Data will be analyzed using SAS® software version 9.4 (SAS Institute, Inc., Cary, NC, USA) and R Statistical Software (The R Project for Statistical Computing).

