### Trial design

We utilized an individual-level, stepped-wedge randomized controlled trial design, with 230 women using traditional wood-burning cookstoves at baseline. Women were randomly assigned into study arms 1 and 2 by blindly drawing a number from a bag at a community meeting. Six repeated measures occurred over the 3-year study period from August 2015 through May 2018 (Table 1). Study arm 1 (*n* = 115) received the *Justa* cookstove intervention after visit 2, and arm 2 (*n* = 115) received the intervention after visit 4 (Table 1). A unique benefit of the stepped-wedge design is that each study arm provides before and after observations, and each arm switches from ‘control’ status to ‘intervention’ status over the course of the study, but not at the same time [31].

**Table 1 Tab1:** Study scheme for timing and visits of interventions, Honduras, August 2015 – May 2018

Stepped-wedge randomized controlled trial		
Timing of study visits for data collection	Arm 1 (*n*=115) Stove type	Arm 2 (*n*=115) Stove Type
Visit 1: Aug – Dec 2015	Traditional	Traditional
Visit 2: Jan – May 2016	Traditional	Traditional
	Arm 1 receives intervention	
Visit 3: Sep – Dec 2016	*Justa*	Traditional
Visit 4: Feb – May 2017	*Justa*	Traditional
		Arm 2 receives intervention
Visit 5: Sep – Dec 2017	*Justa*	*Justa*
Visit 6: Feb – May 2018	*Justa*	*Justa*

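### Eq. (1) and its power simulation assume one constant within-woman correlation over about 30 months, and nothing planned tests this; robust standard errors would be a cheap safeguard

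*Protocol article*

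**What the plan says.** All of this is in the protocol article.

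- **Model.** Under Statistical analysis, Eq. (1) has a fixed effect for assigned stove, a natural cubic spline in visit date, one random effect per participant, and a residual that "is an independent error term".
- **Power.** The same section says the simulated data follow the study design and Eq. (1). For systolic pressure the inputs are an SD of 12 mmHg and "a correlation of 0.76 between repeated measures from the same individual". With one woman in ten lost, the detectable difference at 80% power is put at 1.81 mmHg. No time lag is given for the 0.76. The section reports that power held when linear and seasonal trends were added.
- **Sensitivity analyses.** The ones listed vary the form of the time adjustment (including visit indicators), exclude women on medication or ill, and exclude some air samples. None changes the correlation structure, and robust standard errors are not mentioned.
- **Timing.** Under Trial design, "Six repeated measures occurred over the 3-year study period from August 2015 through May 2018". Arm 1 crosses over after visit 2 and arm 2 "received the intervention after visit 4". The last row of Table 1 is "Visit 6: Feb – May 2018".

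**The concern.** A random intercept with independent errors implies compound symmetry: two readings 5 months apart are taken to be as alike as two readings about 30 months apart. Blood pressure in one person may well drift, so that distant readings agree less.

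The Table 1 spacing makes this relevant. Visits 1–2, 3–4 and 5–6 are each about 5 months apart, while the crossovers fall in the gaps of about 7.5 and 7 months. Close pairs therefore share a stove type, and the before/after contrast leans on the longer lags.

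Two things rest on the assumption: the interval and p-value for β, and the 1.81 mmHg. Because the simulation generates data from the model it then fits, it cannot show what happens if the correlation is not constant. The trends added to the simulation and the planned variations of the spline all change the mean, not the correlation.

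**Working it through.** **Inputs.** 230 women in equal arms, 10% lost: 230 × 0.9 = 207. SD 12 gives variance 144. With ρ = 0.76, the between-woman variance is 144 × 0.76 = 109.44 and the residual variance 144 × 0.24 = 34.56. Visit times at the middle of the Table 1 windows, in months: 0, 5, 12.5, 17.5, 24.5, 29.5 (assumed). Two-sided α = 0.05 is assumed, since none is stated, so the multiplier is 1.960 + 0.842 = 2.802.

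**Step 1: reproduce 1.81 mmHg (constant correlation, linear trend).**

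- Within-woman sum of squares of x: 4 × 2/6 = 1.3333 in either arm.
- For time: mean 14.83, sum of squares 1958 − 6 × 14.833² = 637.8.
- Cross-product: 84 − 4 × 14.83 = 24.67 (arm 1) and 54 − 2 × 14.83 = 24.33 (arm 2), average 24.5.
- Left after removing the trend: 1.3333 − 24.5²/637.8 = 0.3922 per woman.
- Within-woman information: 207 × 0.3922/34.56 = 2.349.
- Between-woman information: mean x is 4/6 or 2/6, so 207 × (1/6)² = 5.75. A woman's six-visit mean has variance 109.44 + 34.56/6 = 115.2, and 5.75/115.2 = 0.050.
- SE(β) = 1/√2.399 = 0.646. Detectable difference = 2.802 × 0.646 = **1.81 mmHg**.

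A 3-df natural cubic spline gives 1.82–1.83 and visit indicators 1.96. The stated figure contains no arithmetic error.

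**Step 2: let the true correlation decay while Eq. (1) is still fitted.** With V the true covariance and W the inverse of the compound-symmetric covariance at the average correlation, let A = ΣX′WX. Then:

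- model variance = A⁻¹
- true variance = A⁻¹(ΣX′WVWX)A⁻¹
- type I error = 2Φ(−1.96 ÷ ratio), where ratio = true/model SE
- power at 1.81 = Φ(1.81/SE_true − 1.96)

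The results below are for 207 women, with ranges covering the linear trend and the 3-df spline. The decay shapes are illustrative assumptions, and small changes in the assumed dates move the second decimal.

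| Assumed correlation | True/model SE | Detectable difference (mmHg) | Power at 1.81 |
|---|---|---|---|
| Constant 0.76 | 1.00 | 1.81–1.83 | 79–80% |
| *0.76 is the adjacent-visit value:* | | | |
| falls linearly to 0.70 | 0.98 | 1.85–1.86 | 78% |
| falls linearly to 0.60 | 0.95–0.96 | 1.91–1.92 | 75–76% |
| falls linearly to 0.50 | 0.94 | 1.97–1.99 | 72–73% |
| AR(1), 0.76 per visit | 0.96–0.97 | 2.34–2.38 | 57–58% |
| exponential, 0.76 per 6 months | 1.02–1.03 | about 2.5 | 52–54% |
| *0.76 is the average over all lags:* | | | |
| 0.80 falling to 0.68 | 0.96 | 1.74–1.76 | 82–83% |
| 0.85 falling to 0.60 | 0.92 | 1.66–1.68 | 86% |
| 0.90 falling to 0.52 | 0.89 | 1.60–1.62 | 88–89% |

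**Step 3: range of the standard-error distortion.** A stable component plus a faster exponential component gives ratios of 1.02–1.08 with a smooth trend, and up to 1.12 with visit indicators (a planned sensitivity analysis). The lowest ratio among all decay shapes tried was 0.85. At 0.85, 1.96/0.85 = 2.31, so type I error is about 2%. At 1.12, 1.96/1.12 = 1.75, so it is about 8%.

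**The case against.** A random-intercept mixed model is a conventional and fully stated choice, and residual covariance is often left to an analysis plan that is not shown here. Field work ended in May 2018 and "The sample size of 230 was selected based on feasibility and cost considerations", so restating power changes no design decision. The distortion of the standard error is modest, its sign depends on a decay shape that nothing in the documents selects, and in many shapes the model errs on the conservative side.

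Most of this stands, and it rules out two stronger readings.

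- **A reader might infer that 1.81 mmHg is too small.** Decay alone does not make it so. It is too small only if 0.76 is a short-lag value. If 0.76 is an average over the study's lags, 1.81 is conservative. The article does not say which applies. The highest figures also need a fall to about 0.25, for which the documents give no basis.
- **A reader might infer that the model's standard errors are generally too small.** The table shows ratios on both sides of 1, more of them below.

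Three points survive. The article writes out the error structure itself, so this is a stated choice and not an omitted detail. Every listed robustness check leaves the correlation untouched. And because the direction of the error cannot be known in advance, a standard error that does not depend on the assumption is worth having. The analysis is described in the future tense, so it can still be added.

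**Conclusion.** The point holds in a limited form. The primary interval and the power figure both depend on a within-woman correlation that stays constant across visits about 5 to 30 months apart, and no planned analysis relaxes this. Under the decay shapes tried, true/model SE runs from about 0.85 to 1.12 and type I error from about 2% to 8%, in either direction.

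The 1.81 mmHg is correct on its own terms. With the same 10% loss and a smooth trend, it becomes about 1.85–2.5 mmHg if 0.76 is a one-visit-lag value that decays, and about 1.6–1.76 if 0.76 is the average over lags. Moderate linear decay from 0.76 to 0.50–0.70 moves it only to 1.85–1.99.

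These figures assume two-sided 0.05, mid-window visit dates, constant variance and illustrative decay shapes. Severity is low: this is a cheap improvement and does not show that the trial is underpowered or the analysis invalid.

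**What to change.** - Report woman-clustered robust standard errors for β in the primary analysis. With 230 independently randomised women these are reliable, and they protect the interval whichever way the correlation behaves.
- Add, at least as a sensitivity analysis, a residual correlation that decays with the time between visit dates, keeping the woman random effect. SAS and R, the named software, both fit this.
- State the time lag to which the 0.76 refers.
- Give the detectable difference as a range over constant and decaying correlation, using the same 10% loss and spline model as the stated 1.81 so that the figures are comparable.

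The cost is some wording, a re-run of the simulation and a little extra analysis; no new data are needed. The stated detectable difference may become less favourable.

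### Both stove installations cross the same spring-to-autumn boundary, the primary model leaves its time spline unsized, and the stated 1.81 mmHg matches only time terms too stiff to remove season

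*Protocol article*

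**What the plan says.** Eq. (1) in Statistical analysis is a linear mixed model with a fixed effect β for assigned stove, a random participant intercept and a smooth function f of visit date. That function is a natural cubic spline, "with the complexity of the adjustment controlled by the number of spline functions". No number is given. Season and visit terms appear only among the sensitivity analyses, which vary the spline size and allow for "considering alternative representations such as indicators of season or visit number".

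Table 1 (Trial design) gives the calendar. Visits 1, 3 and 5 fall in August or September to December; visits 2, 4 and 6 fall in January or February to May. Arm 1 receives the stove after visit 2 (January to May 2016), and its next visit is "Visit 3: Sep – Dec 2016". Arm 2 receives it after visit 4 (February to May 2017), and its next visit is in September to December 2017.

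The power text says "we estimate there will be 80% power to detect a difference of 1.81 mmHg" for systolic pressure after 10% loss. It then adds: "The power remained constant adding linear trends of 3 mmHg/year and seasonal trends of amplitude 3 mmHg to the simulated blood pressure measurements". It states neither the spline size nor the seasonal phase used.

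**The concern.** Visits alternate between two seasons, and both arms change stove across the same spring-to-autumn gap. A slow trend cannot follow that alternation, so part of any seasonal change common to both arms is credited to the stove. Randomisation protects the between-arm contrast at visits 3 and 4, but Eq. (1) also uses before-after information, and that part is exposed.

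β is the primary quantity for all three primary endpoints. If the spline is small, a shared season could create or hide an effect of the size sought. If it is large enough to prevent this, the published detectable difference is too favourable. With the size open, the choice could also be made after the data are seen, among models whose β may differ by more than the target.

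**Working it through.** **Inputs.** From Statistical analysis: "assuming a standard deviation of 12 mmHg for systolic blood pressure", "a correlation of 0.76 between repeated measures from the same individual", 10% loss (taken first as 207 complete women, 103.5 per arm) and a 3 mmHg seasonal amplitude. From Table 1: visit windows, and switches after visits 2 and 4. Assumed because not stated: two-sided alpha 0.05, so the multiplier is 1.960 + 0.842 = 2.802; season equal in both arms; visit dates at window midpoints or uniform within windows.

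**Step 1: information from the concurrent contrast.** Residual variance is 144 × (1 − 0.76) = 34.56. The arms differ in stove only at visits 3 and 4, so z = (0,0,1,1,0,0). With a random intercept and six visits, z′V⁻¹z = [2 − (0.76/4.80) × 4]/34.56 = 1.3667/34.56 = 0.03954. Information is (103.5/2) × 0.03954 = 2.046. With visit indicators this is all the information there is: SE = 1/√2.046 = 0.699, and the detectable difference is 2.802 × 0.699 = **1.96 mmHg**.

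**Step 2: reproduce 1.81.** Let time be linear, with window midpoints 9.5, 14.5, 22, 27, 34 and 39 months from January 2015. The average stove indicator by visit is (0, 0, 0.5, 0.5, 1, 1). Its residual sum of squares on time is 1 − 24.5²/637.83 = 0.0589. This adds 207 × 0.0589/34.56 = 0.353, for a total of 2.399. SE = 0.646, and the detectable difference is **1.81 mmHg**. The published figure therefore reproduces, with about 15% (0.353/2.399) of the information coming from the before-after contrast.

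**Step 3: bias per 1 mmHg of season.** Add 1 mmHg at visits 1, 3 and 5 in both arms. The concurrent contrast is unaffected. The residuals of the average stove indicator at those visits are 0.070, 0.090 and 0.129, summing to 0.288. Bias = (207 × 0.288/34.56)/2.399 = **0.72 mmHg** per 1 mmHg autumn-minus-spring difference. The same calculation gives 0.65 with 3 spline functions, 0.59 with 4, and 0 with visit indicators.

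**Step 4: the article's own season.** A cosine of amplitude 3 mmHg was projected on Eq. (1) for 12 monthly phases (207 women, dates uniform within windows):

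| Time term | Detectable difference (mmHg) | Power at 1.81 | Largest absolute bias (mmHg) | Phases with bias above 1.81 |
|---|---|---|---|---|
| Linear | 1.79 | 80.9% | 3.37 | 8 of 12 |
| 3 functions | 1.81 | 80.0% | 2.99 | 8 of 12 |
| 4 functions | 1.82 | 79.5% | 2.76 | 8 of 12 |
| 5 functions | 1.91 | 75.7% | 0.99 | 0 |
| 6 functions | 1.88 | 76.8% | 1.57 | 0 |
| 7 functions | 1.95 | 74.1% | 0.03 | 0 |
| 8 functions | 1.95 | 74.0% | 0.09 | 0 |
| Visit indicators | 1.96 | 73.5% | 0.04 | 0 |

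At 3 functions the smallest bias on the monthly grid is about 0.7 mmHg. The sign changes with phase, so the bias passes through zero between grid points. If 3 mmHg is peak to trough, every bias figure halves.

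**Step 5: does power stay constant?** The linear trend is no difficulty, since every one of these time terms absorbs it. The season is. At 3 functions (SE 0.646), even a bias of 0.7 moves power for a true 1.81 from 80% to Φ(1.11/0.646 − 1.96) = 40% or Φ(2.51/0.646 − 1.96) = 97%, depending on direction.

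**Step 6: loss pattern and CRP.** If the 10% is progressive dropout, linear to 4 functions give about 1.75 to 1.78 and visit indicators about 1.91 (power 76%). If 10% of visits are missing at random, visit indicators give 1.97. With no loss they give 1.86 (power 78%). Five or six functions give 1.79 to 1.82 only with no loss, which is not the stated condition. For CRP (SD 1.1, correlation 0.66, 207 women), the detectable difference is 0.196 mg/dL with linear time and 0.212 with visit indicators, against a stated 0.2.

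**The case against.** The best reply is that the article fixes no small spline, and that the number of functions is a detail commonly left to an analysis plan. It also simulated a season and planned both varying spline sizes and visit indicators, so a spline that is too stiff would probably be exposed. All of this is fair, and it rules out several stronger readings.

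- A reader might infer that the spline cannot absorb season. It can: about seven functions leave almost no bias.
- A reader might infer that season is fully confounded with the stove. It is not: visits 3 and 4 give a concurrent randomised comparison, which is why visit indicators identify β.
- A reader might take 3 mmHg of bias, or rejection near 100% under the null, as the expected result. Those are worst-phase figures. In 4 of 12 phases the bias is below 1.81, and nothing in the article shows that a 3 mmHg season exists in this population. No seasonal size is given for CRP or HbA1c.
- A reader might extend the change to Aim 2. The exposure there is measured PM2.5, not a randomised step, and no calculation supports it. With windows of four to five months, a date spline may adjust for season better than visit indicators.

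What the reply does not meet is the conflict inside the published text. The article makes the spline primary and visit indicators secondary, and gives a detectable difference that fits only a stiff spline beside a robustness claim that needs a flexible one. If the two analyses disagree, the spline result is the primary one. The power shortfall is modest, and since the sample size was set on feasibility and cost, no design decision depends on it.

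**Conclusion.** The point holds as a conditional one. With about four or fewer functions, a shared season of the article's simulated amplitude biases β by roughly 0.7 to 3 mmHg across monthly phases, above 1.81 in 8 of 12, or about half that if 3 mmHg is peak to trough. With about seven or more functions, or visit indicators, the bias is about 0.2 mmHg or less. At 10% loss, an adjustment that removes season gives a detectable difference of about 1.91 to 1.97 mmHg and about 73% to 76% power at 1.81. The stated 1.81 and the claim of constant power therefore do not fit together, unless the simulated season happened to peak near one of the two phases where the bias cancels.

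The potential bias matters more than the loss of power. The result rests on the assumptions listed with the inputs and on spline knots at quantiles of visit date.

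**What to change.** For the Aim 1 primary analyses, make visit indicators the primary f(t) in Eq. (1), or prespecify a date spline with at least about seven functions. Move date splines with fewer functions to the sensitivity analyses. Leave the Aim 2 models as they are.

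Restate the systolic detectable difference as about 1.9 to 2.0 mmHg (equivalently, about 73% to 76% power at 1.81 with 10% loss) and CRP as about 0.21 mg/dL. State the time term, the seasonal phase and the meaning of amplitude behind the power simulation.

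The cost is a change of wording, using a model already planned, and a systolic detectable difference about 5% to 9% less favourable (1.91/1.81 to 1.97/1.81). No new data are required.
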